### Dose Criteria

Target volume and OAR dose constraints must be adhered to. The planning target goal is for the prescription isodose to encompass at least 95% of the PTV and 99% of the GTV/ITV. Please refer to the SOCRATES HCC QA, RT Planning and Delivery Guidelines for further details.

### Target Volume Definitions

Target volumes must be defined as per ICRU 50, 62 and 83, with clear definitions, individual contouring and specific labeling^(53-55)^. Please refer to the SOCRATES HCC QA, RT Planning and Delivery Guidelines for details.

### Motion Management

A motion management strategy must be utilised for all participants. Various motion management strategies can be used to minimise treatment volumes and reduce dose to normal tissue, and should be selected based on treatment site and participant suitability. Please refer to the SOCRATES HCC QA, RT Planning and Delivery Guidelines for details.

### Treatment Delivery

Treatment must be delivered using a conformal or intensity modulated technique including DCAT, IMRT, VMAT, TomoTherapy or CyberKnife. Beam arrangements, energies, dose rates and other specific approaches are at the discretion of the treating centre. Please refer to the SOCRATES HCC QA, RT Planning and Delivery Guidelines for details.

### Treatment Verification

All patients must undergo daily pre-treatment online imaging verification. Verification imaging must be capable of visualising the target (or surrogate) with soft tissue matching as well as bone alignment. This would necessitate on-board imaging capable of 3-dimensional representation of soft tissue. Fiducial tracking is also acceptable. Please refer to the SOCRATES HCC QA, RT Planning and Delivery Guidelines for details.

### On-Trial Radiotherapy Quality Assurance (RT QA) Program

This trial includes an on-trial RT QA program which consists of the following:

1. Phase 1 Sampling:
   - Pre-Treatment SABR QA Technical Review
   - Post-Treatment (pre-RT sampled) SABR QA Technical Review
2. Phase 2 Sampling:
   - Post-Treatment SABR QA Technical Review

Please refer to the SOCRATES HCC QA, RT Planning and Delivery Guidelines.

## Concomitant and other treatments

Participants may receive any medication that is clinically indicated for treatment of adverse events. All concomitant treatments given, with reasons for the treatment, will be recorded in the CRF.

Information on any concomitant medications and treatment in the 4 weeks prior to randomisation will be recorded.

Prior to confirmation of disease progression (or study withdrawal/completion), subsequent regimens of anti-cancer therapy or other investigational drugs should not be used. After disease progression confirmed, only subsequent regimens of anti-cancer therapy will be recorded in CRF.

## Treatment post progression

After per-protocol progression has been confirmed by central radiological review (please refer to Section 8 DISEASE PROGRESSION and Section 15.7.4 Progression Reviews for further details), treatment will be according to local institutional standard of care. Crossover therapy is permitted.

Where expedited central review is required, the treating team should contact [[contact]](mailto:[contact]) to discuss timelines for data submission and central review.

# TRIAL PARTICIPANT ASSESSMENTS

Patients must provide written, informed consent (Section 5.2 Informed Consent) before any study specific procedures occur.

## Screening

Consenting patients will be assessed to ensure that they meet the trial eligibility criteria (Section 4.3 Eligibility Criteria). Subjects who do not meet these criteria must not be enrolled into the study.

All screening procedures are to be completed as per **Table 5: Schedule of Assessments** and within 28 days of randomisation (unless stated below) and include;

- Demographic and characteristics (including gender and indigenous status)
- Documentation of eligibility for MWA/RFA or TACE/TARE.
- Documentation of Child Pugh status and BCLC staging
- Documentation of viral hepatitis B and C status and treatment
- Medical/surgical history including prior anti-cancer therapies
- Clinical Assessment including;
  - ECOG Performance status
  - Presence of ascites or encephalopathy
  - Weight, height and body mass index
- Concomitant medications (from 4 weeks prior to consent)
- Patient reported outcomes (EORTC QLQ-C30, QLQ-HCC18)
- Disease assessment
  - Abdominal Imaging: Multiphase contrast-enhanced CT or MRI of the liver (See APPENDIX 3: Imaging Guidelines for recommended sequences)
  - Chest imaging: CT chest
- Blood tests:
  - Clinical chemistry: AST, ALT, ALP, GGT, total bilirubin, albumin, creatinine, sodium
  - Haematology: Haemoglobin (Hgb), White Cell Count (WCC), Neutrophil count (Neuts), Lymphocyte count (Lymph), Platelet count (Plts)
  - Coagulation: INR
  - AFP

Once screening procedures have been conducted and the patient’s eligibility has been confirmed, the patients may be randomised into the study (see section **5.4.2 Randomisation Treatment Allocation**).

Treatment interventions are to be commenced within 28 days of randomisation and be completed within the primary therapy window (not more than 42 days from randomisation).

## End of Treatment

To be performed on the last day +/- 2 days of SABR treatment or prior to discharge following each standard of care therapy.

- Clinical assessment including;
  - ECOG Performance status
  - Adverse event reporting (CTCAE v5.0)
  - Concomitant medications
- For the thermal ablation treatments in cohort 1, a post-ablation contrast enhanced CT is required to verify the ablation margin.
  - This is recommended to occur within 24 hours post ablation (see section 6.1.1.1 Quality Assurance (QA) measures for MWA/RFA)

Note: A summary of staff resources used in the planning and delivery/conduct of treatment will be submitted in to the trial database at the End of Treatment visit (as described in **section 14.6.1 Health economics analysis**)

## Follow-up

### 4 weeks Post Treatment (+/- 1 week)

- Blood tests:
  - Clinical chemistry: AST, ALT, ALP, GGT, total bilirubin, albumin, creatinine, sodium
  - Haematology: Hgb, WCC, Neuts, Lymph, Plts
  - Coagulation: PT, APTT, INR
  - AFP
- Clinical assessment including;
  - ECOG Performance status
  - Presence of ascites or encephalopathy and Child Pugh score
  - Weight and body mass index
  - Adverse event reporting (CTCAE v5.0)
    - *Assessment of toxicity is continuous and will include any event occurring between assessments*.
  - Concomitant medications
  - Recording of any additional investigations or events performed or hospitalisations (required for Health economics analysis)
- Patient reported outcomes (QLQ-C30, QLQ-HCC18)
- Invitation for the participant to take part in a telephone interview to talk about their treatment experience in the trial with verbal confirmation of continuing consent
  - If consented, the interview will be conducted by a central designated interviewer within 2 weeks.
  - See **section 10 QUALITATIVE REVIEW OF THE PATIENT EXPERIENCE** for further details.

### Post Randomisation

Visits will occur from 3 months post-randomisation in 3 monthly intervals (+/- 2 week) to 2 years and then 6 monthly (+/- 2week) until completion of the trial and are to include;

- Blood tests:
  - Clinical chemistry: AST, ALT, ALP, GGT, total bilirubin, albumin, creatinine, sodium
  - Haematology: Hgb, WCC, Neuts, Lymph, Plts
  - Coagulation: PT, APTT, INR
  - AFP
- Clinical assessment including:
  - ECOG Performance status
  - Presence of ascites or encephalopathy and Child Pugh score
  - Weight and body mass index
  - Adverse event reporting (CTCAE v5.0)
    - *Assessment of toxicity is continuous and will include any event occurring between assessments*.
  - Concomitant medications
  - Recording of any additional investigations or events performed or hospitalisations (required for Health economics analysis)
- Disease assessment:
  - Abdominal Imaging: Multiphase contrast-enhanced CT or MRI of the liver
    - In the individual patient it is recommended that the same imaging modality is used throughout the study for more reliable response assessment.
    - See **APPENDIX 3: Imaging Guidelines** for recommended sequences.
  - See **Section 8 DISEASE PROGRESSION** for further details on assessment for disease progression.

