## Progression

Once progression has been confirmed on abdominal imaging, completion of restaging with a CT chest (+/- pelvis) is required within 2 weeks.

On-trial assessments should continue beyond progression to allow for collection of subsequent therapies, QoL, and second sites of progression to aid primary and secondary endpoint evaluations. It is expected that the use of further locoregional therapies for new sites of intrahepatic disease relapse outside the original target lesions will be a common event over the course of study.

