## Schedule of Assessments

**Table 4: Schedule of Assessments**

| **ASSESSMENT** | **PRE**  **RANDOMISATION** |  | **END OFTREATMENT** | **FOLLOW UP** | | | | | | | | | | **PROGRESSION^12^** |
| --- | --- | --- | --- | --- | --- | --- | --- | --- | --- | --- | --- | --- | --- | --- |
|  |  |  |  | **Post Treatment** | **Post**  **Randomisation** | | | | | | | | |  |
|  |  |  |  | **4 wks** | **3**  **mo** | **6**  **mo** | **9**  **mo** | **12**  **mo** | **15**  **mo** | **18**  **mo** | **21**  **mo** | **24**  **mo** | **30+**  **mo ^1^** |  |
| **Eligibility confirmation** | ✓ |  |  |  |  |  |  |  |  |  |  |  |  |  |
| **Informed consent** | ✓ |  |  |  |  |  |  |  |  |  |  |  |  |  |
| **Medical History** | ✓ |  |  |  |  |  |  |  |  |  |  |  |  |  |
| **Clinical assessment^2^** | ✓ |  | ✓ | ✓ | ✓ | ✓ | ✓ | ✓ | ✓ | ✓ | ✓ | ✓ | ✓ |  |
| **Concomitant Medications^4^** | ✓ |  | ✓ | ✓ | ✓ | ✓ | ✓ | ✓ | ✓ | ✓ | ✓ | ✓ | ✓ |  |
| **Bloods^5^** | ✓ |  |  | ✓ | ✓ | ✓ | ✓ | ✓ | ✓ | ✓ | ✓ | ✓ | ✓ |  |
| **Hepatitis status^6^** | ✓ |  |  |  |  |  |  |  |  |  |  |  |  |  |
| **Abdominal Imaging ^7,8^** | ✓ |  |  |  | ✓ | ✓ | ✓ | ✓ | ✓ | ✓ | ✓ | ✓ | ✓ |  |
| **Chest Imaging^9^** | ✓ |  |  |  |  |  |  |  |  |  |  |  |  | ✓ |
| **Pregnancy Test^10^** | ✓ |  |  |  |  |  |  |  |  |  |  |  |  |  |
| **Patient Reported Outcomes^11^** | ✓ |  |  | ✓ |  | ✓ |  | ✓ |  | ✓ |  | ✓ | ✓ |  |
| **Adverse Event Reporting**  **(CTCAE v5)** |  |  | ✓ | ✓ | ✓ | ✓ | ✓ | ✓ | ✓ | ✓ | ✓ | ✓ | ✓ |  |
| **Participant experience interview** |  |  |  | ✓**^13^** |  |  |  |  |  |  |  |  |  |  |

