## Adverse event (AE) reporting

### Adverse Events (AE)

Adverse events are to be reported between from consent and 28 days after all the last study treatment [list study treatments] is discontinued and must be graded according to The National Cancer Institute (NCI) Common Terminology Criteria for Adverse Events (CTCAE) version 5.0 by a delegated staff member. For each AE, the highest grade observed since the last visit should be reported on the relevant CRF.

All non-serious adverse events (including anticipated and unanticipated device related adverse events) shall be recorded in the trial database via adverse event CRFs. Internal statistical analysis of these data shall be performed at the times specified in the protocol and investigators and responsible ethical committees will be advised of any safety issues which emerge during this process.

Any AEs that are unresolved at the participant’s last visit in the study are followed up by the investigator for as long as medically indicated, but without further recording in the CRF. The TMC retains the right to request additional information for any participant with ongoing AE(s) at the end of the study, if judged necessary.

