### Serious Adverse Events (SAE)

SAEs are to be reported to the TCC by the trial site within 24 hours of being notified, from consent and within 28 days from the completion of treatment [SABR, RFA, MWA, TARE, TACE] is completed/discontinued.

The investigator at the trial site is responsible for;

- grading the event according to the [NCI CTCAE vs 5](chrome-extension://efaidnbmnnnibpcajpcglclefindmkaj/https:/ctep.cancer.gov/protocoldevelopment/electronic_applications/docs/ctcae_v5_quick_reference_5x7.pdf)
- identifying the seriousness of the adverse event
- identifying the causal relationship to the treatment (see **Table 8: Definitions of causality**)
  - attribution to the SAE must be recorded in the patients’ medical records and reported on the SAE form
- identifying the causal relationship in relation to other medication
- determining the expectedness according to the Investigators Brochure (medicinal products)
- reporting to their local approving authorities as per local guidelines
- to follow-up the event until resolution or death

The initial SAE report should always include at least the following information; participant number, suspected medicinal produce if applicable, identifiable reporting source, description of medical event, seriousness criteria and causality assessment by the investigator. Remaining information must be forwarded to the TCC as soon as possible, but no later than 7 calendar days from the initial report.

The investigator is also responsible for notifying responsible HRECs, Research Governance Officers or other appropriate regulatory authorities of the SAE according to local ethical and regulatory guidelines. They are also to follow up the event (with regular reporting) until resolved.

The trial coordinating centre (TCC) shall;

- Implement and maintain a suitable recording system to record information from all SAEs received from Trial Sites.
- On receipt of an SAE, arrange for the trial chairpersons and/ or a clinical reviewer to review the event and confirm causal relationship and expectedness
- Report all SAEs to TROG Cancer Research
- Notify the sponsor (TROG Cancer Research) and all other participating investigators of any serious unanticipated related adverse events and any action taken
- Notifying the regulatory authorities of each country of any significant issue that has arisen from analysis of overseas reports or action that has been taken by another country’s regulatory authority in reporting timelines.

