## Endpoint Definitions

**Table 8: Endpoint definitions**

|  | **ENDPOINTS** | **MEASURES** |
| --- | --- | --- |
| **PRIMARY:** | 2-year FFLP | Local target lesion progression in Cohort 1 and Cohort 2 defined by mRECIST and RECIST v1.1 as outlined above in Section 8.1 **Definition of Progression*** |
| **SECONDARY:** | 2-year PFS | Local progression or the development of new intrahepatic or extrahepatic lesions as defined in Section 8 DISEASE PROGRESSION |
|  | 2-year OS | Death from any cause |
|  | Safety and adverse events | Cumulative incidence CTCAE v5.0 |
|  | Patient reported outcomes | EORTC QLQ-C30 and QLQ-HCC18 - mean scores over time. Time to ≥10 point decrease in the combined GHS/QoL score. |
|  | Health economic comparisons | Costs cost per QALY gained for SABR compared with PA/SOC at two years |

* If the estimated treatment effects for FFLP are similar for the 2 cohorts we will also perform an additional secondary analysis for FFLP in which data from the 2 cohorts are combined. With 218 patients and an overall event rate of 15% in the combined population, this sample size will provide 90% power to detect a hazard ratio=2.0 at alpha=0.05.

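### The protocol gives two incompatible windows for collecting adverse events and takes no CTCAE symptom grades before treatment

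*Protocol*

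**What the plan says.** **Safety section.** Protocol 13.2.1 states: "Adverse events are to be reported between from consent and 28 days after all the last study treatment [list study treatments] is discontinued". The bracketed treatment list was never filled in. Section 13.2.2 sets the SAE limit as "within 28 days from the completion of treatment [SABR, RFA, MWA, TARE, TACE] is completed/discontinued", and 13.1 builds the same 28 days into the definition of an SAE. For each AE, 13.2.1 asks for the worst grade since the previous visit. A causality assessment is required only for SAEs (13.2.2, Table 7).

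**Visit schedule.** The screening list in 7.1 has no AE or CTCAE item. In Table 4 the row "Adverse Event Reporting" is empty before randomisation and ticked from end of treatment through 30+ months. Section 7.3.2 has visits every 3 months to 2 years and 6-monthly after that until the trial ends, and adds: "Assessment of toxicity is continuous and will include any event occurring between assessments".

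**After progression.** Section 6.5 says "Crossover therapy is permitted". Section 7.4 says "On-trial assessments should continue beyond progression to allow for collection of subsequent therapies, QoL, and second sites of progression". Section 6.4 narrows the recording of concomitant medication at progression to later anti-cancer regimens. No matching rule exists for AEs.

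**Endpoint and population.** Table 8 defines the safety endpoint as "Cumulative incidence CTCAE v5.0". Section 14.5.2 defines the safety set as per-protocol patients who received their assigned treatment for the whole trial.

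**The concern.** The two parts of the protocol disagree on both the start and the end of AE collection, and a site cannot follow both. Each reading has its own cost.

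- **28-day rule.** Radiation effects that appear months later, such as the biliary strictures described in section 1.6, would not be reported for the arm in which they are expected.
- **Visit schedule.** AEs after salvage or crossover are recorded with no attribution, because the only attribution requirement applies to SAEs and an event after the 28 days is by definition not an SAE.
- **Either reading.** No CTCAE symptom grade exists from before treatment. Entry criteria admit Child-Pugh B7, diuretic-controlled ascites and ECOG 2, so some patients will arrive with symptoms that a later visit may record as events.

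This matters because section 1.5 rests the case for SABR on better local control without added toxicity. A diluted comparison makes a finding of no increase easier to reach. The safety committee also reviews safety data every 6 months (14.5.2), whereas the SAP need only be final before data lock (14.6).

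**Working it through.** The plan states no figure for this point, so the main check compares its own sections. The arithmetic that follows is illustration under stated assumptions.

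**1. Start of collection.** 13.2.1: consent. 7.1 and Table 4: nothing before end of treatment. These conflict.

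**2. End of collection.** Treatment must be complete within 42 days of randomisation (section 6), so the 28-day rule closes by day 42 + 28 = 70 at the latest. The 3-month visit falls at about day 91, or day 77 at the early edge of its 2-week allowance. No event starting after day 70 would be reportable under 13.2.1, yet Table 4 has AE ticks at every visit from 3 to 30+ months and 7.3.2 includes events between visits. These conflict, unless crossover therapy counts as study treatment. The unfilled placeholder leaves that open, and 13.2.2 names the modalities without saying whether crossover use is meant.

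**3. What is known at baseline.** Section 7.1 collects ascites, encephalopathy, Child-Pugh, ECOG, history, chemistry, haematology and INR, so these can be graded in retrospect. CTCAE grades for symptoms such as fatigue, pain and nausea are not collected.

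**4. Dilution.** Let b be the share of patients in each arm with a counted finding already present, and p the true rate of new events. The observed rate is b + (1-b)p, so the observed difference is (1-b)(p2 - p1). Take 5% (upper SABR grade ≥3 rate, section 1.4) against 16% (16.1% grade 3 for RFA in the randomised proton trial cited there), with 59 per arm, a two-sided 5% test of two proportions, and b assumed:

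| b | Observed rates | Difference, points | Power |
|---|---|---|---|
| 0% | 5.0% vs 16.0% | 11.0 | 50% |
| 10% | 14.5% vs 24.4% | 9.9 | 27% |
| 20% | 24.0% vs 32.8% | 8.8 | 18% |
| 30% | 33.5% vs 41.2% | 7.7 | 14% |
| 40% | 43.0% vs 49.6% | 6.6 | 11% |

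**5. Post-progression harm.** The section 14.1 assumptions imply 2-year local failure of 5% vs 25% (Cohort 1) and 10% vs 35% (Cohort 2). The arm sizes are 47/0.80 = 59 and 40/0.80 = 50, as stated. Ignoring dropout and death, the expected numbers of local failures are:

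- Cohort 1: 0.05 × 59 = 3 vs 0.25 × 59 = 15
- Cohort 2: 0.10 × 50 = 5 vs 0.35 × 50 = 17.5

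Let t be the same true toxicity in both arms (assumed 5-10%), s the share of local failures re-treated (assumed 50-100%) and x the harm from re-treatment (5-16%). The observed rate is t + (1-t)·f·s·x, where f is the local failure rate, so the false excess in the control arm is (1-t)(f2 - f1)·s·x.

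- Cohort 1 low: 0.90 × 0.20 × 0.5 × 0.05 = 0.45 points; high: 0.95 × 0.20 × 1.0 × 0.16 = 3.0 points
- Cohort 2 low: 0.90 × 0.25 × 0.5 × 0.05 = 0.56 points; high: 0.95 × 0.25 × 1.0 × 0.16 = 3.8 points

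The upper ends amount to about 2 patients per arm (0.030 × 59 = 1.8; 0.038 × 50 = 1.9).

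**The case against.** A reader might infer that the toxicity comparison is biased in favour of SABR because it counts pre-existing cirrhosis findings and salvage harm against the randomised arm. The documents do not support that.

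- **Nothing says these events are counted that way.** If 13.2.1 governs, most harm after crossover is never collected. Section 14.5.2 may also drop patients who cross over. That stands. It is not a full remedy, because removing patients by crossover removes them by local failure, which the design expects to differ by arm. It also sits uneasily with the general intention-to-treat statement in 14.6.
- **Most cirrhosis findings are recorded at screening.** This stands for laboratory values, ascites, encephalopathy, Child-Pugh and ECOG. The baseline QLQ-C30 and QLQ-HCC18 also show whether fatigue, pain or nausea was present, but they are not CTCAE grades.
- **The AE definition needs an untoward occurrence linked in time to treatment.** A stable condition that was present before treatment does not plainly qualify. That is fair, but no text sets such conditions aside and no baseline grade exists against which to judge worsening.
- **Randomisation balances pre-existing findings on average.** This stands: they dilute the comparison and do not favour an arm.
- **Counting rules belong in the SAP.** A rule for new or worsened events can be written there, and its absence here is no fault. The SAP cannot recreate grades never taken or events never reported.
- **Counting all harm after a first-line strategy, salvage included, is a legitimate comparison.** This stands, so there is no case for making a cut at first subsequent therapy the main safety analysis.

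**Conclusion.** The firm finding is an internal contradiction: sections 13.1 to 13.2 and sections 7.1, 7.3.2 and Table 4 give different start and end points for AE collection, and the placeholder that might settle the end point is blank. The second finding is narrower: CTCAE symptom grades are missing at baseline and cannot be recovered.

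Dilution takes a true difference to (1-b) of its size in both arms alike. The values of b are assumed, since the protocol gives no baseline prevalence, and the calculation supposes that every pre-existing finding is counted at the grade compared. Post-progression harm could differ by arm by about 0.5 to 3.8 points. That range rests on the planned failure rates, the assumed re-treatment share and equal true toxicity. Its upper harm rate comes from one trial in recurrent disease whose grade 3 events were transient. It largely disappears if the 28-day limit governs.

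This is a worthwhile, inexpensive correction to a secondary endpoint. A bias towards SABR is not shown.

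**What to change.** (a) Tick the AE row in the pre-randomisation column of Table 4, add baseline CTCAE grading to 7.1, and count events that are new or worse than the baseline grade.

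(b) Reconcile 7.3.2 and Table 4 with 13.1, 13.2.1 and 13.2.2 so that a single AE window applies. Fill the placeholder and state whether crossover therapy counts as study treatment. If the window is kept short, say how late radiation effects will be captured; if it runs to the end of follow-up, say what attribution is needed for events outside the SAE period.

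(c) Record each AE's date relative to the first subsequent anti-cancer therapy, so that events before and after it can be tabulated separately alongside the overall comparison. Section 6.4 already has those regimens recorded.

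The cost is one form page at an existing screening visit, edits to a few sentences, and a small amount of extra tabulation.
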